### Secondary Outcomes and Analysis

One of the secondary hypotheses of this trial is whether the binary outcome described above of habit formation is associated with positive changes in behavioral automaticity using the SRBAI. Behavioral automaticity is the hypothesized key MoBC for this trial. A Fisher exact test (5%, 2-sided) will be used to examine whether an hourly walking habit formation will be associated with positive changes in behavioral automaticity. Specifically, for each participant, the difference between average behavioral automaticity during the last 2 weeks of intervention and average baseline behavioral automaticity will be calculated; a positive change is defined as a difference of greater than zero. Additionally, we will model the association between habit and continuous changes in automaticity over time using autoregressive models of order 1 to account for serial autocorrelation between repeated measures of the SRBAI. Finally, a mixed-effects logistic regression will be used to assess the effects of behavioral automaticity on the development of a daily walking habit, with adjustment for other factors, such as caregiver demographic characteristics and factors related to caregiving. For this model, we will examine the fixed effects of automaticity, time, and the time-by-automaticity interaction effect to examine whether changes in automaticity over time are associated with habit formation.

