
### Sample Size Calculation

A sample of 100 participants is planned for enrollment into this remote trial. Up to 20% attrition is expected following the 2-week baseline period due to failure to meet wearable device and survey adherence requirements (n=20). An additional 25% attrition is expected after the 10-week intervention period due to participants becoming lost to follow-up, withdrawing, or other (n=20). The expected attrition throughout the intervention period is estimated as such because of the burdens caregivers experience due to the nature of their unique responsibilities, not limited to time constraints and motivation, which may produce barriers to longitudinal research participation [87]. We have attempted to design this trial to minimize barriers to participation for caregivers specifically, yet have estimated attrition similar to that in other longitudinal physical activity trials with caregivers to be conservative [88,89].

The trial still will have a sufficient sample (n=60) to provide adequate power. Assuming a null habit formation rate of 30% with a sample size of n=60, a 1-sided, one-sample binomial test at 5% significance will have about 92% power to declare the BCT intervention effective if the true habit formation rate is at 50% or above. We believe the null hypothesis for habit formation is conservative, as caregivers spend 80% of their time being sedentary.

To anticipate the variability due to the proposed total sample size of 60, we calculated the power to detect a difference between 20% habit formation (in the group of participants without increased behavioral automaticity) versus 60% habit formation (in the group of participants with increased behavioral automaticity) under different scenarios. Specifically, when 30% of the participants experience an increase in behavioral automaticity, there is 86% power to detect the difference. When 50% of the participants experience increases in behavioral automaticity, the power increases to about 89%.

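### The 86% and 89% power figures for the automaticity–habit test overstate the planned two-sided Fisher test (83.5% and 85.1%), and neither scenario matches the 50% habit rate assumed for the primary outcome

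*Protocol article*

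**What the plan says.** All references are to the Protocol article.

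- **Planned test.** Secondary Outcomes and Analysis: "A Fisher exact test (5%, 2-sided) will be used to examine whether an hourly walking habit formation will be associated with positive changes"; the changes meant are those in SRBAI score. Each participant is classed by comparing mean SRBAI in the last two intervention weeks with the baseline mean, and "a positive change is defined as a difference of greater than zero".
- **Power for that question.** Sample Size Calculation: "To anticipate the variability due to the proposed total sample size of 60, we calculated the power to detect a difference"; the rates compared are 20% (no increase in automaticity) and 60% (increase). It then says that "when 30% of the participants experience an increase in behavioral automaticity, there is 86% power to detect the difference". For an even split it says: "When 50% of the participants experience increases in behavioral automaticity, the power increases to about 89" percent. No test, alpha or sidedness is attached to these two figures.
- **Primary power.** The paragraph just before, also for n=60, takes a null habit rate of 30% and claims about 92% power, one-sided at 5%, if the true rate is 50% or more.
- **Other automaticity analyses.** Secondary Outcomes and Analysis also plans a first-order autoregressive model of continuous automaticity change and a mixed-effects logistic model. Weekly logistic and isotonic regressions on SRBAI follow.

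**The concern.** Two things do not fit together.

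First, a reader will take the 86% and 89% as the power of the planned two-sided Fisher test, because it is the only two-group test the article sets out for this question. Fisher's test is conservative in samples this small, and its power at these inputs is lower than stated.

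Second, the share of participants who increase, together with the two habit rates, fixes the overall habit rate. That is the quantity the primary outcome tests. If the overall rate implied by the mechanism scenarios differs from the one behind the primary power, the article has not shown that 60 participants give the stated power for both aims at once. Automaticity is the trial's hypothesized key mechanism, so the mechanism test should be powered under a scenario in which the primary hypothesis is true.

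**Working it through.** **Inputs.** From Sample Size Calculation: n = 60; habit rate 0.60 with an increase and 0.20 without; share increasing 30% (18 v 42) or 50% (30 v 30); primary null 0.30 and alternative 0.50. From Secondary Outcomes and Analysis: Fisher exact test, two-sided, 5%.

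**Step 1. Where the stated figures can come from.** The two-sided pooled normal approximation is

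power = Φ[(0.40 − 1.96·se0)/se1], with se0 = √{p̄(1−p̄)(1/n1+1/n2)} and se1 = √{0.24/n1 + 0.16/n2}.

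- 18 v 42: p̄ = 0.32, se0 = 0.1314, se1 = 0.1309, so Φ(1.088) = 86.2%.
- 30 v 30: p̄ = 0.40, se0 = 0.1265, se1 = 0.1155, so Φ(1.317) = 90.6%.

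Other methods, by full enumeration unless noted:

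| Method | 18 v 42 | 30 v 30 |
|---|---|---|
| Stated in the article | 86% | about 89% |
| Pooled normal approximation, two-sided | 86.2% | 90.6% |
| Uncorrected chi-square, two-sided | 87.7% | 90.5% |
| Arcsine approximation, two-sided | 85.1% | 90.5% |
| Mid-p Fisher, two-sided | 84.9% | 87.2% |
| Fisher, one-sided 5% | 87.6% | 90.9% |
| **Fisher, two-sided 5% (planned)** | **83.5%** | **85.1%** |

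Several standard methods come within about 2 points of both stated figures. None of them is the planned test.

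**Step 2. Power of the planned test.** Enumerate every pair (a, b) and sum Bin(a; n1, 0.60) × Bin(b; n2, 0.20) over the pairs whose two-sided Fisher p-value is at most 0.05.

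- 18 v 42: 83.5%, which is 86 − 83.5 = 2.5 points below the stated figure.
- 30 v 30: 85.1%, which is 89 − 85.1 = 3.9 points below.

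If group sizes are random (binomial with the stated share) instead of fixed, Fisher power is 81.5% and 86.7%, also below the stated figures.

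**Step 3. Implied overall habit rates.**

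- 30% increasing: 0.30×0.60 + 0.70×0.20 = 0.32.
- 50% increasing: 0.50×0.60 + 0.50×0.20 = 0.40.

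The primary calculation does reproduce: rejecting at 25 or more of 60 has exact one-sided alpha 3.6% and power 92.2% at a true rate of 50%. Under the same rule, the chance of primary success is 7.3% at a true rate of 32% and 44.4% at 40%.

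**Step 4. The scenario that agrees with 50%.** Keep 60% and 20% and solve 0.60s + 0.20(1 − s) = 0.50. This gives s = 0.30/0.40 = 0.75, so 45 v 15. Enumeration as in step 2 gives two-sided Fisher power of 75.5%.

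**Step 5. How far this depends on the 60%/20% pair.** Other pairs can also average 50%. As an illustration of my own, an even split with rates of 70% and 30% keeps the 40-point difference and has overall rate 0.5×0.70 + 0.5×0.30 = 0.50. Fisher power there is 83.8%. The 75% figure therefore holds for the article's own pair of rates, not for every scenario with a 50% overall rate.

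**The case against.** **The figures can be reproduced.** Sample Size Calculation attaches no test to them, and ordinary approximations land within about 2 points. The primary power in the same section is one-sided, so a one-sided basis here is plausible too. This stands. A reader might infer a plain arithmetic error, and the article does not support that. What remains is a mismatch with the planned test, and both corrected values are still above 80%.

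**The scenarios are only scenarios.** The 50% is the alternative at which the primary test is powered. It is not a forecast that binds every secondary calculation, and nobody claims the primary test is powered at 32% or 40%. The article also promises no particular power for the mechanism test at a 50% overall rate. This stands as far as it goes: it is an inconsistency of planning assumptions, not a formal error. It does not explain why no scenario agrees with the primary hypothesis.

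**Cutting the change at zero.** A reader might go further and conclude that the split wastes information and that a rank test on the continuous change should replace Fisher. The article does not support that. It already plans several models that use automaticity without this cut. Nor is a rank test clearly better. With 30%, 50% and 75% increasing, a simulation in which habit log-odds are linear in a normally distributed change gives Wilcoxon 96%, 98% and 96% power, against 82%, 87% and 73% for Fisher. If habit rates instead step from 20% to 60% at zero, Wilcoxon falls to 67%, 79% and 53%, against 82%, 87% and 74%. The ranking turns on a shape that the article does not fix.

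**Conclusion.** The point holds in a limited form. Under the planned two-sided 5% Fisher exact test, the stated powers are too high by 2.5 and about 4 points (83.5% and 85.1%, against 86% and about 89%). Both listed scenarios also sit at overall habit rates, 32% and 40%, below the 50% on which the primary power rests. With the article's own 60% and 20% rates, the case that matches 50% has about 75% power and is not shown.

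This rests on 60 analysed participants, fixed group sizes at the stated shares, and the two habit rates as given. It does not show that the sample size is wrong or that the Fisher test should be replaced.

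**What to change.** In Sample Size Calculation:

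1. State that the secondary power is for the two-sided 5% Fisher exact test.
2. Restate it as about 83% (30% increasing) and 85% (50% increasing).
3. Add a scenario whose overall habit rate is 50%. With 60% and 20% retained, that is 75% of participants increasing (45 v 15), with about 75% power. If the team considers another pair of rates more realistic, give that pair and its overall rate.

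The cost is one recalculation and a few sentences, in the statistical analysis plan or a note to the protocol, before the analysis expected in Fall 2026. The price is an openly stated power below 80% in one scenario. The planned Fisher test, the continuous-automaticity models and the enrolment target stay as they are.

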## Results

### Recruitment Status

This National Institute on Aging–funded trial was awarded in June 2024. The trial is designed to enroll participants on a continuous, rolling basis. Recruitment and data collection began in March 2025. Forty ADRD caregiver participants (40% of the planned sample) have been enrolled as of August 2025. No major deviations from the original protocol have occurred. We expect to complete data collection by June 2026. Data analysis of primary, secondary, and exploratory outcomes is expected to be complete by Fall 2026. Deidentified raw datasets along with data dictionaries, and the trial protocol and statistical analysis plan will be posted on the trial’s Open Science Framework page at the time of publication of results. We expect to publish results by Winter 2026. Results will be posted with the trial registration on ClinicalTrials.gov in accordance with policy.

## Discussion

### Principal Results

This NIH Stage II decentralized behavioral trial has the potential to advance science on forming a habit to disrupt sedentary behavior among caregivers for persons with ADRD and will help determine whether behavioral automaticity acts as the primary MoBC for the effect on this BCT intervention to form an hourly walking habit. If successful, this trial will inform further NIH Stage III effectiveness trials, can be applied to other ADRD populations, and can be applied to other physical activity behaviors, such as moderate activity interventions. Although out of scope for this trial, additional areas of exploration should also include objective confirmation of sedentariness and maintenance of habit formation to understand whether hourly walking habits persist long-term and beyond delivery of the intervention.

### Potential Limitations

A limitation of this trial includes possible issues with the generalizability of the study findings. Based on the demographic makeup of caregivers of people with ADRD across the United States, a majority female sample is expected [7]. A second limitation is that this trial was not designed to capture nonwalking sedentary interruptions, such as periods of standing, by nature of the research objective, and the use of Fitbit wearable devices to collect continuous data. While there is some evidence that disrupting prolonged sitting behavior with standing has positive health associations, the positive health outcomes associated with disrupting sedentary behavior with walking are much more demonstrated and understood in the literature, hence the focus of this efficacy trial [90-94]. A third limitation is that we identified behavioral consistency for hourly walking (eg, walking 250 steps per h for 4 consecutive h and for 7 days in a row) as a definition for our primary outcome of habit formation. This metric was used to allow us to use a dichotomous measure of habit formation while also capturing the time duration required to achieve formation of habit. However, multiple additional criteria could easily be used to determine the presence or absence of habitual behavior. We will also be measuring daily steps longitudinally over the full duration of the trial to address this. Additional limitations may be with SMS text message fatigue, intervention fatigue, and/or low participant engagement, all of which could subsequently lead to missing data, as caregivers are a population who already experience burden and so may have barriers to completing the trial successfully. Our trial is intentionally designed with caregivers’ unique needs in mind (eg, no in-person study visits, use of electronic survey data capture, and personalized intervention times). We also intentionally designed the trial to deliver the daily components of the BCT intervention using concise language and as behavioral “nudges” that do not require engagement (eg, a response) from the participant to reduce perceived messaging or intervention fatigue. Yet, it may still be that participation is not feasible for all caregivers. Strategies will be implemented to alleviate perceived challenges of participating in the research throughout the trial, including weeknight and weekend clinical research staff support for caregivers who may only be available outside of standard business hours, providing caregivers the option to pause participation due to unanticipated circumstances and resume at a better time, and, if the caregiver wishes to withdraw from the research, offering caregivers the option to partially withdraw by passively providing only Fitbit data (rather than fully withdraw). Additionally, we have statistical methods and sensitivity analyses to manage missing data as described in the Methods section.

### Conclusions

This trial represents an opportunity for advancement in knowledge about the effectiveness of forming a habit using BCTs to disrupt sedentary behavior in caregivers of persons living with ADRD, and “how” they work via the hypothesized MoBC behavioral automaticity. Based on the literature, remotely delivered, easily administered behavior interventions focusing on habit formation have the potential to create behavior change, and trial designs intended to minimize perceived challenges may provide opportunities for future effectiveness trials to create public health impact to promote physical activity.
